### Study population and setting

The target population will consist of women aged 60 years and older residing in urban and rural areas of Khafr County, located in Fars Province, Iran, all of whom will be registered at urban and rural comprehensive health service centers. The inclusion criteria will be the absence of psychiatric disorders, cognitive impairment (Mini-Cog screened), balance disorders, and gait problems (tandem gait screened), willingness to participate in the study, and provision of informed consent. Individuals experiencing bereavement within the past 6 months and those missing at least one intervention session will be excluded from the study.

To maintain the integrity of the study results, participants should avoid enrolling in any formalized group activities with similar aims to the study interventions, such as scheduled walking clubs, guided meditation sessions, or therapeutic nature programs, for the duration of the 8-week intervention phase. There are no restrictions on standard medical care or informal daily routines.

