## Materials and methods

### Study design

This study is designed as a three-arm, parallel-group, randomized controlled trial (RCT) within a superiority framework. It aims to evaluate the superiority of two nature-based interventions, walking with meaningful conversations and group meditation in an open natural environment, over a no-intervention control condition, on cognitive empowerment and mental vitality in older women (Fig. 1). A multistage cluster sampling method will be used for participant recruitment. Eligible participants will be randomly assigned to one of the two intervention groups or a control group (Fig. 1). This study will be conducted in nine main phases: (1) Preparation phase: including obtaining ethical approvals, training, and coordinating the research team; (2) screening: the initial phase for identifying participants and recruiting volunteers; (3) informed consent: obtaining consent from participants for study enrollment; (4) randomization allocation: randomly assigning participants to the intervention and control groups; (5) baseline assessment (pretest): to measure cognitive empowerment and mental vitality; (6) conducting an intervention: participants in the intervention groups receiving the two intervention methods and the control group receiving routine health care; (7) post-intervention assessment (posttest): conducted immediately after the intervention to evaluate short-term effects; (8) follow-up phase: 3 months post-intervention to examine the long-term sustainability of the intervention effects; and (9) data analysis: data entry and statistical analysis, interpretation of results, and dissemination of findings.

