### Intervention

The interventions will consist of eight sessions, each lasting 120 min, held 3 days a week in an outdoor natural setting. Including 1 h of travel time, each session will last approximately 3 h. To facilitate participation, round-trip transportation will be arranged by the researcher using a bus service from local health centers to the session venue. Participants will gather at their assigned health center and will be returned there after each session. Each intervention session will be supervised by the researcher, accompanied by two trained health liaisons. These liaisons, local community health volunteers, will assist in ensuring participant safety, responding to concerns, and supporting effective engagement during each session. Participants will be advised to bring appropriate outdoor clothing, comfortable footwear, water, and any necessary medications. The researcher will use a session checklist to ensure all protocol components (e.g., warm-up, 50-min core activity, and discussion) are delivered. Participant attendance and engagement will be recorded.

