### Control group

The control group will not receive any specific intervention during the study period. Instead, the participants will continue to receive standard care and support from their local healthcare centers. This approach will allow for a comparative analysis of the effects of the interventions by assessing differences in outcomes between the intervention and control groups. However, to ensure that control group participants also benefit from similar activities, they may be invited to participate in comparable sessions after the completion of the study. To adhere to ethical considerations and prevent feelings of disappointment or neglect in the control group, the following provisions will be considered:Provision of information and counselingMembers of the control group will receive comprehensive counseling regarding their health and well-being challenges. This counseling will include guidance on effective self-care and quality of life.Invitation to participate in future activitiesUpon completion of the main intervention, members of the control group may be invited to participate in similar activities. These activities will include educational sessions or social programs designed to promote participants’ health and awareness after the study concludes.Review and provision of resultsAt the end of the study, the overall research findings will be presented to all participants (both intervention and control groups). This action will foster a sense of involvement and value among participants and will provide them with information regarding the impact of the interventions.Creation of learning opportunitiesFollowing the intervention, educational sessions on topics related to mental and physical health in older adulthood will be organized for the control group. This will provide them with the opportunity to benefit from similar experiences, thereby upholding the ethical principles of the research in a way that ensures all participants, including members of the control group, will gain from their participation.

The following diagram will illustrate the anticipated impact of the interventions on mental health and cognitive empowerment in older adults. The walking group with meaningful conversation is expected to demonstrate greater improvements in mental vitality, whereas the meditation group is expected to show more progress in cognitive empowerment. The control group is expected to experience fewer changes (Fig. 2).

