### Data collection

Data collection will be conducted in a structured and systematic manner to ensure the reliability and validity of the results. This process will begin with the acquisition of the necessary ethical and administrative approvals prior to any data collection activities. The study will also be registered with the Iranian Registry of Clinical Trials (IRCT20241023063481N1). To ensure data quality, all research personnel received standardized protocol training. The researcher will visit the selected health centers, explain the objectives and methodology of the study to the managers and healthcare staff, and obtain their consent to cooperate. Following this, the process of informing potential participants will begin. Assessments occur at three time points: baseline (pre-intervention), immediately post-intervention (week 8), and at a 3-month follow-up. At each stage, outcome measures (cognitive empowerment, mental vitality) are collected. To uphold the intention-to-treat principle, all participants initially randomized will be included in the final analysis. Individuals who choose to discontinue the active intervention sessions will still be invited to provide outcome data at the designated follow-up assessments (week 8 and 3 months), subject to their ongoing consent for this limited study involvement. Copies of all paper-based data collection forms are retained as study records and are available for review upon reasonable request.

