### Statistical methods

To assess the homogeneous distribution of confounding variables across the three groups before the intervention, the chi-square test was used for categorical variables, and one-way ANOVA was applied for continuous variables. All analyses will follow the intention-to-treat principle. Missing data (up to 14%) will be imputed using regression methods.

The primary analysis will test the superiority of the interventions on the primary outcome: change in cognitive empowerment score at week 8. To account for multiple comparisons, the significance level for the three pre-planned between-group comparisons (walking vs. control, meditation vs. control, walking vs. meditation) will be adjusted using the Bonferroni correction, resulting in a corrected alpha of 0.0167.

Changes in outcomes over time, between groups, and their interaction will be analyzed using the generalized estimating equation (GEE) model. Baseline individual and clinical variables showing significant between-group differences (e.g., age, marital status, physical activity) will be included as covariates to control for potential confounding. Analyses for secondary outcomes will be considered exploratory.

All analyses will be conducted using Stata version 17, with a two-tailed alpha level of 5% for tests not covered by the primary correction. Graphs will be generated using GraphPad Prism version 8.

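### Excluding any woman who misses one session removes participants after randomisation, in the two active arms only, and contradicts the intention-to-treat commitment

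*Protocol article*

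**What the plan says.** Study population and setting lists two grounds for exclusion in one sentence: recent bereavement, and attendance ("those missing at least one intervention session will be excluded from the study"). The attendance ground carries no qualification. It is not tied to a secondary analysis, and it makes no allowance for the reason a session was missed.

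Two later sections say something different. Data collection states that "all participants initially randomized will be included in the final analysis", and adds: "Individuals who choose to discontinue the active intervention sessions will still be invited to provide outcome data at the designated follow-up assessments". Statistical methods states: "All analyses will follow the intention-to-treat principle". It then says how gaps will be filled: "Missing data (up to 14%) will be imputed using regression methods".

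Three other sections determine where the attendance rule can act:

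- Study design numbers the phases. Phase "4) randomization allocation: randomly assigning participants to the intervention and control groups" comes before the intervention, which is phase 6.
- Intervention: "The interventions will consist of eight sessions, each lasting 120 min".
- Control group: "The control group will not receive any specific intervention during the study period".

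Criteria for modifying or stopping the intervention does not name a missed session.

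**The concern.** Attendance cannot be an eligibility criterion, because it is not known until after allocation. Here it would work as a post-randomisation exclusion, and an asymmetric one: a control has no session to miss and can never be removed by it.

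If the rule is applied, the two active-versus-control comparisons set women with perfect attendance against an unselected control arm. Perfect attenders are probably healthier and more motivated, so the likely direction favours the interventions. The walking-versus-meditation comparison is also affected if absence differs between those arms.

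The wording goes beyond dropping someone from one analysis. If site staff take a woman out of the study after a missed session, her week-8 score may never be collected, and no later analysis plan can restore the intention-to-treat set. If the contradiction stays open, the choice between the two rules could also be made once attendance and results are known.

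**Working it through.** **1. The texts side by side.** Take a woman allocated to walking who misses session 3. Under Study population and setting she is out of the study. Under Data collection and Statistical methods she is in the final analysis. No sentence says which rule prevails.

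**2. Inputs from the protocol.** 37 women per arm, so 74 in the active arms and 111 in all; 8 sessions; 20% attrition allowance; calculated effect size 0.41 (Sample size); imputation for up to 14% missing data and a corrected alpha of 0.0167 (Statistical methods). The effect size reproduces from the stated means and SDs: (28.3 − 27.5) / √((1.8² + 2.1²)/2) = 0.8 / 1.956 = 0.409. It serves below only as a yardstick.

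**3. Inputs assumed.** The protocol gives no attendance rate and no correlation between attendance and outcome. Both are assumed and shown over a range.

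**4. How many women the rule would remove.** With attendance probability p per session and independent absences, the probability of attending all eight is p⁸.

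| p | p⁸ | Left of 37 per active arm | Removed of 74 | Controls removed |
|---|---|---|---|---|
| 0.98 | 0.851 | 31.5 | 11.0 | 0 |
| 0.95 | 0.663 | 24.5 | 24.9 | 0 |
| 0.90 | 0.430 | 15.9 | 42.1 | 0 |
| 0.85 | 0.272 | 10.1 | 53.8 | 0 |

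**5. Absence rates at which the plan's own allowances are used up.**
- 20% attrition within the active arms: 1 − 0.80^(1/8) = 2.8% absence per session.
- 14% missing within the active arms: 1 − 0.86^(1/8) = 1.9%.
- 14% missing across the whole trial: 0.14 × 111 = 15.5 women, which is 21% of 74, so 1 − 0.79^(1/8) = 2.9%.

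**6. Size of the selection effect.** Suppose a normally distributed tendency to attend has correlation r with the outcome, and only the upper fraction P = p⁸ is kept. The mean of those kept shifts by r·φ(z)/P SD, where z is the cut-off.
- p = 0.95: φ(z)/P = 0.365/0.663 = 0.550. The shift is 0.11 SD at r = 0.2 and 0.17 SD at r = 0.3.
- p = 0.90: φ(z)/P = 0.393/0.430 = 0.913. The shift is 0.18 SD at r = 0.2 and 0.27 SD at r = 0.3.

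**7. Type I error.** One active-versus-control t-test was simulated with no true effect, 37 randomised per arm and selection in the active arm only (20,000 runs per setting). At nominal 0.0167, the error rate was as follows.

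| Excluded from the active arm | r = 0.2 | r = 0.3 | r = 0.5 |
|---|---|---|---|
| 14.9% (p = 0.98) | 0.019 | 0.023 | 0.033 |
| 33.7% (p = 0.95) | 0.027 | 0.041 | 0.086 |

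**8. Sensitivity to clustered absences.** If some women are habitually absent, more of the rest attend every session. A beta-binomial model with an assumed within-woman correlation of 0.2 keeps 79% at p = 0.95, 61% at 0.90 and 47% at 0.85. The step 6 shifts for r = 0.2 to 0.3 become 0.07 to 0.11 SD at p = 0.95 and 0.13 to 0.19 SD at p = 0.90.

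**The case against.** The best defence is that the sections on analysis are explicit and should govern analysis, while the attendance clause sits in an eligibility paragraph. Read that way, all 111 women are analysed and there is no bias. That is a fair account of what may have been intended, and it makes the harm conditional. It does not remove the conflict: the clause speaks of exclusion from the study, and staff who follow it would stop collecting the data that the analysis sections need.

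Four points on size stand in part:

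- Independent absences and a stable tendency to attend do not sit well together. Clustering lowers both the losses and the shifts (step 8), so the independent-absence figures are towards the upper end.
- The primary outcome is a change from baseline. A fixed difference between attenders and others largely cancels in a change score; only a correlation with change biases it. The range 0.2 to 0.3 for r has no source in the protocol.
- The direction is inferred. On a scale bounded at 25 and 75, women who start higher have less room to improve.
- The protocol plans transport, weekly reminders and family support, which should raise attendance. Even so, about 2.8% absence per session uses up the attrition allowance in the active arms if absences are independent.

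It is also true that the follow-up promise covers women who choose to discontinue and is subject to their consent, and that a woman who misses one session has not discontinued. The contradiction therefore rests mainly on the two sentences requiring analysis of everyone randomised.

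**Conclusion.** The concern holds. The protocol states two incompatible rules about who remains in the trial, and one of them selects on post-randomisation behaviour in the active arms alone. This follows from the text and needs no assumption.

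The numerical consequences do need assumptions: that the exclusion is applied, that attendance lies somewhere between 85% and 98% per session, and that attendance is related to the change in score. On those terms the active arms could lose from about 15% to over 70% of their women under independent absences, and fewer if absences cluster. The selection shift at 90% to 95% attendance could plausibly run from under 0.1 SD to nearly 0.3 SD. A shift of that order is a material part of a planned effect of 0.41. The true size cannot be derived from the protocol. Because the primary comparison is at stake and lost outcome data cannot be recovered later, this should be corrected before recruitment.

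**What to change.** In Study population and setting, delete the clause that excludes women who miss a session, leaving the bereavement criterion in place. Keep every randomised woman in outcome follow-up at week 8 and 3 months, subject to her consent, and in the primary analysis in her allocated arm, as Data collection and Statistical methods already require.

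If the investigators want an estimate among attenders, use the attendance that the Intervention section says is recorded. Label it as a sensitivity analysis, for example a complier-average effect or an analysis by number of sessions attended. Relabelling the rule as the definition of a secondary per-protocol set would also reconcile the text, provided it no longer stops follow-up.

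The cost is a one-line amendment, with no change to the sample size. The estimated effect may be slightly diluted by women who attended less.

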### Criteria for modifying or stopping the intervention

A participant’s assigned activity may be changed or stopped for the following reasons:

Voluntary withdrawal: If a participant asks to leave the studyHealth and safety: If an injury, adverse event, or new health problem makes continued participation unsafeSession adjustments: During sessions, facilitators will reduce walking intensity or allow meditation posture changes if a participant shows discomfort.

### Requirement

To recruit volunteers, a public and targeted call for participation will be disseminated throughout the nine urban and rural health service centers. This call will aim to inform potential participants about the study and the initial inclusion criteria, providing them with general information to facilitate informed decision-making regarding their participation, based on an understanding of the research objectives and involvement requirements. The call for participation will include details regarding the study title and purpose, general inclusion criteria, duration and format of participation, benefits and incentives for participating, and contact information for registration or further inquiries. This call will be disseminated through various informational methods, including the placement of posters, the organization of introductory meetings, and the distribution of informational messages from the urban and rural comprehensive health service centers.

Upon receiving expressions of interest in participating in the study, volunteers will be screened according to the inclusion criteria by initial interview to assess health history, balance test (Additional File 1), and a Mini-Cog test. Volunteers whose scores on these assessments fall within acceptable ranges will proceed to the next stage of the study. Following screening, comprehensive research information will be provided to eligible participants. This information will include detailed explanations of the study objectives, research methodology, participant commitments, the benefits of study participation, potential risks and limitations, and the right to withdraw from the study at any stage without any consequences. To ensure complete understanding among volunteers, all questions will be addressed.

The principal investigator obtained written informed consent from each participant in person. Following this, the same researcher conducted a face-to-face interview to collect baseline data, which included completing the cognitive empowerment and mental vitality questionnaires. This process will continue until the required sample size is achieved. In this way, all participants will enter the intervention simultaneously, since the study will be a group intervention.

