### Additional assessments

Additional baseline assessments comprise the Mini-Cog test for cognitive screening, the Tandem Gait Test for evaluating balance and gait, and a structured form to collect demographic and clinical data.

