### Balance Test (Tandem Gait Test)

Tandem Gait Test is a simple, noninvasive test used to assess dynamic balance in older adults. It involves walking in a straight line, placing the heel of one foot directly in front of the toes of the other foot. The test is performed in a flat, unobstructed area, and safety measures are taken to prevent falls. The test results are categorized as normal or abnormal based on balance, accuracy, and stability. (Additional File 1).

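### The eligibility tests, including a balance test with a recognised fall risk, are placed before risks are explained and before consent is taken

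*Protocol article*

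**What the plan says.** Study design lists nine phases in order. The second and third are "2) screening: the initial phase for identifying participants and recruiting volunteers; (3) informed consent: obtaining consent from participants for study enrollment". Randomization is the fourth phase and baseline assessment the fifth.

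The recruitment section (Requirement) gives the detail. A public call goes out first, "providing them with general information to facilitate informed decision-making regarding their participation". Women who respond are then "screened according to the inclusion criteria by initial interview to assess health history, balance test (Additional File 1), and a Mini-Cog test". Those with acceptable results move on: "Following screening, comprehensive research information will be provided to eligible participants". That later information is where the section first lists "potential risks and limitations, and the right to withdraw from the study at any stage without any consequences". Consent follows: "The principal investigator obtained written informed consent from each participant in person". The baseline questionnaires come after consent.

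The section on the Tandem Gait Test describes heel-to-toe walking on a flat, clear surface and adds that "safety measures are taken to prevent falls". The Additional assessments section states: "Additional baseline assessments comprise the Mini-Cog test for cognitive screening, the Tandem Gait Test for evaluating balance and gait".

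**The concern.** A volunteer undergoes these tests because she has expressed interest in the trial, and no section presents them as routine care. They are therefore trial procedures. One of them is a physical test in women aged 60 or over, and the protocol sees enough risk of falling to call for precautions.

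In the written order, the explanation of risks and the freedom to withdraw comes after that test and goes only to women who have passed it. Women with an abnormal gait or Mini-Cog result leave before that point. They include those most likely to be unsteady or cognitively impaired. At stake is participant protection: the usual safeguard of informing and asking before a research procedure is reversed for the step that needs it. The statistical results are not at stake.

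**Working it through.** The document gives no figure for this point, so the check compares the sections.

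**1. Order of steps.**

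| Step | Study design | Requirement |
|---|---|---|
| General information | not listed | public call |
| Interview, balance test, Mini-Cog | phase 2 (screening) | after expression of interest |
| Full information with risks and right to withdraw | not listed | after screening, eligible women only |
| Written consent | phase 3 | after full information |
| Baseline questionnaires | phase 5 | after consent |

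The two sections agree that screening precedes consent. The point therefore rests on an order stated twice, not on a detail that an article might leave out.

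**2. What women know before the tests.** The listed content of the call is the title and purpose, general inclusion criteria, duration and format, benefits and incentives, and contact details. Risks and the right to withdraw are not on that list and first appear in the post-screening information. Responding to the call is not described as consent.

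**3. Which test carries a physical risk.** Only the tandem gait test does. Its section calls it simple and noninvasive and provides for fall precautions. The interview and the Mini-Cog carry no fall risk, but they do collect health and cognitive information.

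**4. Are the tests really done before consent?** The Additional assessments section calls the Mini-Cog and the Tandem Gait Test baseline assessments, and the recruitment section places baseline data collection after consent. Read alone, that label could suggest testing after consent. Three places point the other way:
- Study population and setting uses both tests as screens for entry.
- Requirement makes acceptable results the condition for moving to the next stage.
- Study design places baseline assessment after randomization, too late for an eligibility test.

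The pre-consent placement is the operative one, and the label conflicts with it.

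**5. Who is affected.** Every screened woman is. Since all enrolled women pass through screening, the minimum is 111. The protocol gives no screen-failure rate. As an illustration only, assumed rates of 20% and 40% give 111 / (1 − 0.20) ≈ 139 and 111 / (1 − 0.40) = 185 women screened. Of these, 139 − 111 = 28 and 185 − 111 = 74 would leave before the information and consent step. The conclusion does not depend on these rates.

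**The case against.** The strongest reply is that the phase list concerns consent for enrolment. A verbal or short consent for screening may exist in the full protocol or in consent papers that are not shown. That is possible, so a flat statement that women are tested without any consent would go too far. What stands is that the text gives an order, mentions no screening consent, and places the explanation of risks after the tests. If a screening consent exists, one clause settles the matter. If not, the procedure has to change.

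Several stronger readings are tempting, but the document does not support them:

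- *Women are tested with no information.* The public call reaches them first, partly through introductory meetings. What they lack is the comprehensive information.
- *All the screening procedures are hazardous.* Only the tandem gait test has a fall risk, and it is done with precautions.
- *A fall at screening falls outside the safety reporting.* In Handling adverse events, the request to report discomfort is tied to sessions. The sentence on serious incidents, which names a fall as its example, is not limited in that way and can be read to cover screening.
- *Data on women who fail screening are kept without consent.* No section says whether such data are retained, and Statistical methods does not name either test in an analysis.
- *A known number of women go unasked.* The range of 28 to 74 comes entirely from assumed failure rates.

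**Conclusion.** The concern holds in this form: following the protocol as written, the health-history interview, tandem gait test and Mini-Cog are done before risks and the right to withdraw are explained and before written consent is taken. Women who fail these tests never reach either step. The one physical risk involved is the fall risk of the tandem gait test, which the protocol itself recognises.

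The order applies to all 111 enrolled women and to every screen failure, in a number the document does not give. The conclusion assumes that the written order will be followed and that no undescribed screening consent exists. The study flow chart and the SPIRIT schedule are not visible here and could not be checked. The baseline label in Additional assessments is a separate inconsistency that must be reconciled with the recruitment section.

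This is a matter of participant protection and should be corrected before recruitment, which Trial status reports as not yet started. It has no bearing on the sample size, endpoints, randomization or analysis.

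**What to change.** - In Study design and Requirement, move the information on risks and the right to withdraw, together with written consent, ahead of the interview, the tandem gait test and the Mini-Cog. A short written consent limited to screening would also serve. Confirm full trial consent once eligibility is known.
- In Additional assessments, state that the two tests are screening tests done under that consent, or otherwise reconcile the baseline label with the recruitment section.
- Optionally, state in Handling adverse events that the logging of discomfort also covers screening.

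The cost is a reordering of the text and a change to the consent form. The principal investigator already takes consent in person, so no further staff are implied. The small downside is explaining the study to some women who then prove ineligible.
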